The prospect of retarding the progression of Alzheimer’s disease with easily available and inexpensive drugs like NSAIDs is very attractive. Unfortunately, treatment with NSAIDs in the elderly is hampered by their toxicity and related serious side effects, including gastrointestinal bleeding and ulcers.

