## Discontinuation of treatment

- The patient decides to withdraw from the study.
- Presence of serious adverse events related to the study medication.
- Questionable compliance of the patient.
- Intake of systemic corticosteroids for more than two weeks.
- The patient develops a severe and unstable disease (see also exclusion criteria).
- The diagnosis of Alzheimer’s disease is no longer plausible considering the course of the disease.
- Breaking of the medication code.

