# Randomization

Patients participating in the trial will be assigned a sequential trial number. The computer-generated list of trial numbers is linked to a randomized list with medication numbers, equivalent to 80 batches of indomethacin and 80 batches of placebo. The participating pharmacist will retain the randomization code. This procedure warrants a well-balanced initial randomization. However, a difference in the number of patients will occur when patients are withdrawn from the trial. The number of patients withdrawn from the indomethacin group will provide significant information in the final analysis of the data (“intention to treat”).

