## Measures taken in case of adverse events

An adverse event is any undesirable sign, symptom or medical condition occurring after starting the intake of the trial medication, whether considered drug-related or not. Medical conditions/diseases present before starting the trial medication are only considered adverse events if they worsened after starting the medication.

In case of an adverse event with a possible causal relationship to the use of indomethacin, the medical attendant (e.g. family physician, physician) will discontinue the trial medication. The trial ends, however the trial code will not be broken and the patient’s data will be analyzed. The medical attendant will be asked to report this decision to the investigators as soon as possible.

The medical attendant is allowed to lower the dose of the study medication, in case of a dubious causal relationship between the adverse event and the study medication. The trial code will not be broken and the patient will be considered a normal participator of the trial.

In case of a serious adverse event, the patient’s medical attendant will ask the pharmacist to announce the nature of trial medication. The code will then be broken, the medication will be discontinued and the patient’s data will not be included in the analysis of the final outcome measures. However, the data of patients discontinuing the trial will analyzed according to the “intention to treat” principle.

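### Section 10.3 excludes patients with a serious adverse event from the final outcome analysis and also invokes intention to treat, without saying which governs the primary ADAS-cog comparison

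*Protocol*

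**What the plan says.** Section 10.3 sorts adverse events into cases and gives each its own consequence for the data.

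- **Possibly related adverse event.** Medication stops. The text reads "The trial ends, however the trial code will not be broken and the patient", and goes on to say that the patient's data are analysed.
- **Doubtful relation.** The dose may be lowered. The patient stays blinded and counts as an ordinary participant.
- **Serious adverse event.** The "medical attendant will ask the pharmacist to announce the nature of trial medication". The code is broken, medication stops, and the patient's "data will not be included in the analysis of the final outcome measures". No condition of relatedness to the drug is attached.

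The sentence directly after the exclusion begins "However, the data of patients discontinuing the trial will analyzed according to the" and names the intention-to-treat principle.

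Section 8 (Randomization) expects that "a difference in the number of patients will occur when patients are withdrawn from the trial". It then says: "The number of patients withdrawn from the indomethacin group will provide significant information in the final analysis of the data", again with intention to treat in brackets. There the term is attached to a count of withdrawals and does not define who is analysed.

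**The concern.** A patient with a serious adverse event has also discontinued, so two adjacent sentences in section 10.3 apply to the same person and point in opposite directions. One leaves the patient out and the other keeps the patient in. The phrase about final outcome measures is attached to the rule that leaves the patient out. An analyst following the text could therefore reasonably drop these patients from the primary ADAS-cog comparison.

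That exclusion would depend on something that happens after randomisation and may be caused by the treatment. It would also be applied after the patient's allocation is known. The two retained groups would no longer be the groups that were randomised. If the excluded patients decline at a different rate from the rest, and the excluded shares differ between arms, the estimated treatment difference moves for reasons unrelated to efficacy. The retained data alone could not show the size or the sign of that movement.

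**Working it through.** **1. The plan's own figure.** Section 12.1 gives a 3.0-point difference, SD 7.0, one-sided alpha 0.05 and 80% power, and states 67 per group. Check: n = 2 × [7.0 × (1.645 + 0.842) / 3.0]² = 67.3 per group, which matches the stated 67 apart from rounding. The SD of 7.0, the 3.0-point target and the 80 randomised per group are used below.

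**2. The rules side by side (section 10.3).**

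| Reason for stopping | Code broken? | Data in the analysis? |
|---|---|---|
| Possibly related adverse event | No | Yes |
| Serious adverse event | Yes | No (exclusion clause); yes (next sentence, if it covers these patients) |

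The only group whose data are removed is the one whose allocation has been revealed.

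**3. Formula for the shift.** Let p_I and p_P be the shares excluded from the indomethacin and placebo arms. Let g be the number of ADAS-cog points by which excluded patients decline more than retained ones, taken as equal in both arms. In each arm, mean decline of all randomised = mean decline of retained + p × g. Taking placebo minus indomethacin:

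shift in favour of indomethacin = g × (p_I − p_P)

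If g differs by arm, the shift is p_I × g_I − p_P × g_P.

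**4. Illustrative values.** The protocol gives neither the shares nor g, so all of these are assumptions. The last column is the one-sided error rate when there is truly no difference among all randomised patients. It equals Φ(shift / SE − 1.645) with SE = 7.0 × √(1/n_I + 1/n_P), where n_I and n_P are the retained numbers and all retained patients are assumed to have a score.

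| Excluded, indomethacin vs placebo | Patients excluded | Retained | Shift for g = 2 / 4 / 6 | One-sided error for g = 2 / 4 / 6 |
|---|---|---|---|---|
| 5% vs 5% | 4 vs 4 | 76 vs 76 | 0 / 0 / 0 | 5.0% / 5.0% / 5.0% |
| 10% vs 5% | 8 vs 4 | 72 vs 76 | 0.1 / 0.2 / 0.3 | 6.0% / 7.1% / 8.3% |
| 15% vs 5% | 12 vs 4 | 68 vs 76 | 0.2 / 0.4 / 0.6 | 7.0% / 9.6% / 12.9% |
| 20% vs 5% | 16 vs 4 | 64 vs 76 | 0.3 / 0.6 / 0.9 | 8.2% / 12.7% / 18.8% |

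Worked example, 10% vs 5% with g = 6: shift = 6 × 0.05 = 0.3; SE = 7.0 × √(1/72 + 1/76) = 1.15; 0.3 / 1.15 − 1.645 = −1.38; Φ(−1.38) is about 8.3%.

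**5. Sign.** If excluded patients decline less than the rest, g is negative and the shift works against indomethacin: g = −2 at 10% vs 5% gives −0.1, and g = −6 at 20% vs 5% gives −0.9.

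**The case against.** The strongest defence is that the word However, which opens the second sentence, either overrides the exclusion or adds an intention-to-treat analysis beside one without serious-event patients. Section 8 points the same way. That reading is possible, so it would be too strong to say that the sentences cannot coexist. But the protocol does not describe two analyses, and under either reading it does not say which is primary. The defect stands in that form.

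The document does not support several stronger inferences.

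- **That the rule does remove more indomethacin patients.** The Introduction says that "treatment with NSAIDs in the elderly is hampered by their toxicity and related serious side effects, including gastrointestinal bleeding and ulcers", and section 8 singles out withdrawals from the indomethacin group, so an imbalance is plausible. No serious-event rate by arm is given. The 20% in section 9.4 covers all gastrointestinal side effects, and its tenfold figure concerns high-dose indomethacin taken together with corticosteroids. Omeprazole in both arms (section 9.2) and the exclusion of patients with earlier ulcer or bleeding (section 5.3) may narrow any gap. Unrelated serious events in either arm also trigger the rule.
- **That intolerant patients in general drop out of the analysis.** Patients stopped for a possibly related event that is not serious keep their data in the analysis, as do those whose dose is lowered. Only serious events trigger the clause.
- **That sections 5.4 and 10.3 conflict on who stops.** Section 5.4 does list "Presence of serious adverse events related to the study medication", which looks narrower than section 10.3. But it also lists breaking of the code, and section 10.3 breaks the code for every serious event. The two sections therefore lead to the same patients stopping, and section 5.4 says nothing about the analysis set.

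It is also fair to object that including these patients helps only if they have scores. ADAS-cog is scheduled at baseline, week 26 and week 52 (Appendix II), and nothing expressly provides for assessment after medication stops. A patient who stops before week 26 may have no change score. This limits what a change of wording alone achieves, and the fix has to address it.

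**Conclusion.** The point holds. Section 10.3 states an exclusion from the final outcome analysis next to an intention-to-treat commitment, and nothing in the protocol settles which one decides who enters the primary ADAS-cog comparison. This conclusion rests on the text alone and does not need unequal event rates.

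The numerical consequence is illustrative only. Under the assumed shares and extra declines, the shift runs from zero to 0.9 points, or up to 30% of the 3.0-point target (0.9 / 3.0). The milder 10% versus 5% case gives 0.1 to 0.3 points, or about 3% to 10% of the target. The shift is zero with equal shares and the same g in both arms, and zero if excluded patients decline like the rest. Its sign reverses if they decline less. The document supports neither a particular size nor a firm direction of bias.

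**What to change.** 1. In section 10.3, remove only the clause stating that the patient's "data will not be included in the analysis of the final outcome measures". Leave the code-break and medication-stop wording in the same sentence untouched.
2. State that the primary analysis includes all randomised patients in their assigned group and uses all ADAS-cog data collected, whether or not a serious adverse event occurred or the code was broken.
3. State that the week 26 and week 52 ADAS-cog assessments are still sought after medication stops, where the patient agrees.
4. If an analysis without serious-event patients is wanted, keep it as a labelled sensitivity analysis.
5. Make intention to treat in section 8 refer to the set defined in step 2.

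The cost is a change of protocol wording, some assessment visits after discontinuation, and possibly a slightly more variable estimate. Retaining these patients removes the shift only as far as their ADAS-cog scores are actually obtained.

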## Exclusion criteria

- The patient satisfies the NINDS-AIREN criteria for probable vascular dementia, including:
- presence of focal signs on neurological examination consistent with stroke
- evidence of relevant cerebrovascular disease by brain imaging (CT and/or MRI made within two years before the baseline visit)
- A known exaggerated pharmacological sensitivity or allergy to NSAID’s.
- History of peptic ulceration, gastric surgery or gastrointestinal bleeding.
- Current diagnosis of active peptic ulceration.
- Current diagnosis of severe and unstable cardiovascular disease.
- Current diagnosis of renal failure (creatinin > 200 mol/l).
- Advanced, severe and unstable disease of any type, other than Alzheimer’s disease, that may interfere with primary and secondary variable evaluations, including a medical condition which should be expected to progress, recur, or change to such an extent that it may bias the assessment of the clinical or mental status of the patient to a significant degree or put the patient at special risk.
- Intake of any of the following concomitant medications:
- salicylates
- coumarin derivatives
- ACE-inhibitors
- loopdiuretics
- Intake of any of the following concomitant medications more than two months immediately prior or during the study:
- NSAID’s
- systemic corticosteroids
- Intake of any of the following concomitant medications with a possible effect on cognition:
- estrogen
- deprenyl
- vitamin E
- neuroleptics
- anticholinergics

Patients using stable doses of cholinesterase inhibitors were eligible, with the provision that the dose should not be changed during the study. Cholinesterase inhibitors could not be initiated during the study

- Excessive use of alcohol (> 5 units/day)
- The patient is, either alone or with the aid of a caregiver, not able to reliably take the medication.

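### Section 10.3 excludes patients with a serious adverse event from the final outcome analysis, which contradicts its own intention-to-treat sentence

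*Protocol*

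**What the plan says.** Protocol section 10.3 (Measures taken in case of adverse events) has separate rules for two kinds of event.

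- **Possibly drug-related event.** Study drug is stopped. "The trial ends, however the trial code will not be broken", and the patient's data are analysed.
- **Serious adverse event, with no condition on cause.** "The code will then be broken, the medication will be discontinued". On the analysis, the rule is that such "data will not be included in the analysis of the final outcome measures".

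The sentence right after the serious-event rule says that "the data of patients discontinuing the trial will analyzed according to the" intention-to-treat principle. It makes no exception for serious events or unblinding.

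Section 5.4 (Discontinuation of treatment) lists both "Presence of serious adverse events related to the study medication" and "Breaking of the medication code" as reasons to discontinue.

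Two other places bear on the question. Section 8 (Randomization) expects withdrawals from the indomethacin group to inform the final analysis and refers to intention to treat. Section 12.3 (Statistical methods) compares the ADAS-cog change of every patient between the groups and defines no analysis sets.

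**The concern.** The protocol does more than leave the analysis set open for a later document. It states an exclusion rule and then a rule that reverses it. An analyst who obeys one sentence departs from the other, and the choice could be made after the results are known.

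The exclusion is the harmful instruction of the two. It depends on something that happens after randomisation and that the treatment can cause: the Introduction says NSAID treatment in the elderly is hampered by "their toxicity and related serious side effects, including gastrointestinal bleeding and ulcers". If more patients are removed from the indomethacin arm, and those patients would have declined at a different rate from the rest, the comparison of ADAS-cog change is no longer between the groups formed by randomisation.

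**Working it through.** **Step 1: are the excluded patients discontinuers?** Section 10.3 stops their drug and breaks their code. Section 5.4 lists code breaking as a reason for discontinuation, whatever the cause of the event. So every excluded patient is a discontinuer. The converse fails: section 5.4 also lists patient decision, questionable compliance, corticosteroid use and other reasons. The excluded patients are a subset of those whom the next sentence analyses, and a subset is enough for a contradiction.

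**Step 2: the plan's own figure.** Section 12.1 gives SD 7.0, a difference of 3.0 points, one-sided 0.05 and 80% power. The normal formula gives n = 2 × [7.0 × (1.6449 + 0.8416) / 3.0]² = 67.3 per group, which agrees with the stated 67. The SD and the 67 are used below.

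**Step 3: size of the bias if the exclusion is followed.** Let p1 and p0 be the shares excluded on indomethacin and placebo, and let excluded patients in both arms deteriorate d points more than the rest. With no true difference between the groups as randomised, the mean deteriorations of the remaining patients (mA on indomethacin, mP on placebo) satisfy mA + p1·d = mP + p0·d. So

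bias towards indomethacin = mP − mA = (p1 − p0) × d.

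The protocol gives neither serious-event rates nor d, so both are assumptions. The 20 percent in section 9.4 is for gastrointestinal side effects in general, not serious events. The standard error at 67 per group is 7 × √(2/67) = 1.209. Rejection rates are for a one-sided 5% t test with 132 degrees of freedom (noncentral t).

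| Excess excluded, p1 − p0 | d (points) | Bias (points) | Share of 3.0 | Rejection with no true difference |
|---|---|---|---|---|
| 2 percentage points | 1 | 0.02 | 0.7% | 5.2% |
| 3 percentage points | 2 | 0.06 | 2.0% | 5.5% |
| 5 percentage points | 3.5 | 0.175 | 5.8% | 6.7% |
| 10 percentage points | 7 | 0.70 | 23.3% | 14.3% |
| 5 percentage points | −3.5 | −0.175 | −5.8% | 3.7% |
| any | 0 | 0 | 0% | 5.0% |

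The second and third rows are the central cases. A simulation with 80 per group and no other dropout agrees: 8% against 5% excluded with d = 2 gives 5.6%, and 10% against 5% with d = 3.5 gives 6.8%. Keeping every patient gives 4.9% to 5.0%, but only because every simulated patient has an outcome value.

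**Step 4: what inclusion costs.** If the share p1 of the indomethacin arm that stops drug after a serious event gains nothing, a true 3.0-point effect becomes 3.0 × (1 − p1). The share needed here is p1 itself, not the excess p1 − p0. At an assumed 7% it is 3.0 × 0.93 = 2.79 points, and at 15% it is 3.0 × 0.85 = 2.55 points. With 80 per group the standard error is 7 × √(2/80) = 1.107, and one-sided power falls from about 0.85 to about 0.81 and 0.74.

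**The case against.** The strongest reply is that the protocol already means to include these patients. The sentence after the exclusion begins with a contrast and invokes intention to treat, section 8 does the same for withdrawals, and section 12.3 speaks of every patient. On that reading no bias arises. These places do favour inclusion, but the exclusion is still there in plain words and is attached to the final outcome measures. One could also suppose that two analyses are meant, but the text never says so. Analysis sets are commonly left to a statistical analysis plan. Here, however, the protocol has itself fixed a rule and contradicted it.

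The second reply is that the numbers rest wholly on assumptions. That stands. The protocol excludes patients with "History of peptic ulceration, gastric surgery or gastrointestinal bleeding" and gives omeprazole in both arms, so a large excess of serious gastrointestinal events is not the natural expectation. Unrelated events that are equally frequent in both arms add nothing to p1 − p0.

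A reader might infer more than the document supports:

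- **That the rule would inflate the false-positive rate severely.** The 0.70 points and 14.3% need an excess of 8 patients in 80 and a d of one full SD. They mark the edge of the range and are no basis for the severity of the point.
- **That the bias must favour indomethacin.** Its sign depends on d, which is unknown.
- **That excluded and discontinuing patients are one and the same group.** The inclusion runs one way only.
- **That the automatic code break should change too.** Nothing shown here ties it to a harm in the ADAS-cog comparison once those patients are kept in the analysis.

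**Conclusion.** The contradiction is certain from the text: section 10.3 both excludes and includes patients with a serious adverse event. Its numerical consequence is uncertain and probably modest, about 0.06 to 0.18 ADAS-cog points towards indomethacin (2% to 6% of the 3.0-point target). This rests on an assumed excess of 3 to 5 percentage points excluded and an assumed d of 2 to 3.5 points, equal in both arms. The case for correction does not depend on the size: the protocol should not give two opposite rules for who enters its primary comparison. It should be corrected, but it does not by itself invalidate the trial.

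**What to change.** Make two changes in section 10.3.

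1. Delete the exclusion clause. State that all randomised patients, including those who stop study drug or are unblinded, are analysed for ADAS-cog in the group to which they were randomised.
2. Add one general sentence covering both the serious-event and the possibly-related paragraphs: stopping study drug or breaking the code does not end follow-up, and the scheduled week 26 and 52 assessments are kept where the patient agrees. This replaces the words in the possibly-related paragraph that end the trial for the patient. The sentence has to be general because those words do not occur in the serious-event paragraph; replacing them there alone would leave serious-event patients without a follow-up rule.

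The code-break rule can stay as it is.

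No patients or procedures are added, since the week 26 and 52 visits are already in the Appendix II schedule, but patients off drug must be asked to attend. The statistical price is the dilution in step 4: a true 3.0 points becomes 2.79 to 2.55 at an assumed 7% to 15% stopping drug, with power of about 0.81 to 0.74 against 0.85. Some bias may also remain where assessments after the event are missing.

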# Monitoring procedures

## Monitoring of adverse events

Adverse events, whether volunteered by the patient, discovered during questioning by the investigator, or detected through physical examination (vital signs, symptoms of edema) or laboratory evaluation (haemoglobin, white blood cell count, platelet count, creatinine, glucose, liver parameters), will be recorded on the Adverse Event case report form and followed carefully until they resolve. Abnormal laboratory values or test results are not generally considered adverse events, unless they induce clinical signs or symptoms or require therapeutic intervention. An interim analysis of adverse vents will take place twice a year (see *12.4 Interim analysis*).

## Monitoring of compliance

The investigator will record the amount of dispensed trial medication. At each scheduled visit, all returned medication will be examined by the investigator to determine the number of unused capsules, and to determine if the medication used conforms to the amount expected. The information on missing doses will be recorded on the CRF. Also, the patient and caregiver will be questioned about the intake of trial medication.

# Statistical considerations

## Sample size

For estimation of the required sample size, the following assumptions were made:

- patients deteriorate 5.0 points (SD 7.0) on the ADAS-cog in one year.
- a difference of 3.0 points or more regarding the changes from baseline is considered to be clinically relevant in case indomethacin is tested against placebo.
- power of 80 percent.
- statistical testing will be done one-sided, at a significance level of 0.05.

Based on the above statistical considerations, a total of 67 patients per group will be necessary. Assuming a dropout rate of 20 percent, the total sample size will be 160 patients (80 patients per group).

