## Statistical methods

In the final analysis of the results a so-called “evaluation of increment” will take place. Change in ADAS-cog score (primary outcome measure) of every patient will be compared between two groups by means of a 2 x 2 ANOVA (categories: group, time;  = 0.05).

Secondary outcome measures will be analyzed following the same procedure, with correction for multiple equations.

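### The sample size rests on a one-sided 0.05 test, but the ANOVA named for the primary analysis does not carry that direction over; with its ordinary F-test, power at 67 per group is about 69%, not 80%

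*Protocol*

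**What the plan says.** Protocol section 12.1 (Sample size) lists its assumptions. For the expected course it takes it that "patients deteriorate 5.0 points (SD 7.0) on the ADAS-cog in one year". For the effect sought, it holds that "a difference of 3.0 points or more regarding the changes from baseline is considered to be clinically relevant". The target is set as "power of 80 percent", and the test is specified in these terms: "statistical testing will be done one-sided, at a significance level of 0.05". From these inputs the section concludes that "a total of 67 patients per group will be necessary". The allowance for losses then reads: "Assuming a dropout rate of 20 percent, the total sample size will be 160 patients (80 patients per group").

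Protocol section 12.3 (Statistical methods) describes the primary analysis. Each patient's change in ADAS-cog "will be compared between two groups by means of a 2 x 2 ANOVA", with group and time as the factors and a significance level of 0.05. The section does not say one-sided or two-sided, and it does not say how a directional test would be taken from the ANOVA. It also does not say which two visits are the levels of time; the evaluation schedule in Appendix II has ADAS-cog at baseline, week 26 and week 52.

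**The concern.** The usual test in an ANOVA is the F-test, and an F-test has no direction: it rejects for a large difference either way. With two groups and one degree of freedom, F is the square of t, so an F-test at 0.05 is the same as a two-sided t-test at 0.05. The sample size was derived for a different and easier test, one that spends the whole 5% on benefit.

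Two things are at stake. If the F-test is what is run, the stated 80% power does not belong to it. In addition, the protocol leaves two possible success thresholds for the primary outcome. A difference in favour of indomethacin with a two-sided p between 0.05 and 0.10 is positive under 12.1 and negative under the F-test. If that is not settled before the code is broken, the threshold can be chosen with the result in view.

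**Working it through.** **Inputs, all from section 12.1:** difference d = 3.0 points; SD of one-year change s = 7.0; power 80%; alpha 0.05, one-sided; 67 per group required; 80 per group enrolled; 20% dropout.

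**Assumption for steps 1 to 5:** the comparison is of change from baseline to week 52. With time taken as baseline and week 52, the group-by-time effect in the 2 x 2 ANOVA is exactly this comparison.

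**Step 1. Reproduce the plan's figure.** n per group = 2 (z_alpha + z_beta)² s² / d².
- One-sided 0.05: 2 × (1.645 + 0.842)² × 49 / 9 = 67.3. The stated 67 is reproduced (68 if rounded up).
- Two-sided 0.05: 2 × (1.960 + 0.842)² × 49 / 9 = 85.5, so 86.

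The 67 therefore depends on the one-sided test.

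**Step 2. Power at the sizes in play.** The standard error of the difference is s √(2/n). Power is from the noncentral t with 2n − 2 degrees of freedom and noncentrality d / SE. At n = 67, SE = 7 × √(2/67) = 1.209 and the noncentrality is 3.0 / 1.209 = 2.48.

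| Evaluable per group | Where it comes from | One-sided 0.05 | Two-sided 0.05 |
| --- | --- | --- | --- |
| 64 | 80 less 20% | 77.8% | 67.2% |
| 67 | stated requirement | 79.5% | 69.2% |
| 80 | all enrolled are analysed | 85.4% | 76.9% |
| 86 | two-sided, normal formula | 87.6% | 79.8% |
| 87 | two-sided, t-based | 87.9% | 80.3% |

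The normal approximation at 67 gives 79.8% one-sided and 69.9% two-sided, so the choice of formula moves the answer by less than a point.

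**Step 3. Separate sidedness from dropout.** At the stated 67, sidedness alone accounts for 79.5% falling to 69.2%. The 64-per-group row adds a different shortfall. Enrolling 80 matches 67 × 1.2 = 80.4, whereas dividing by the retained fraction gives 67 / 0.8 = 83.75, so 84. After 20% dropout from 80, 64 remain, and power is already 77.8% one-sided.

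**Step 4. Detectable difference, two-sided, 80% power, 64 per group.** (1.960 + 0.842) × 7 × √(2/64) = 2.802 × 1.237 = 3.47, about 3.5 points.

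**Step 5. The band where the thresholds disagree.** At 64 per group (126 degrees of freedom) the critical t is 1.657 one-sided and 1.979 two-sided. Multiplied by SE 1.237, these are 2.05 and 2.45 points. If the observed SD is 7.0, a benefit between those values passes one test and fails the other.

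**Step 6. The other reading of time.** If the two levels are weeks 26 and 52, the group effect is on the average of two changes. Its variance is s² (1 + r) / 2, where r is the correlation between the two changes. The protocol gives neither r nor a week-26 difference. As an illustration only, assume SD 7.0 at both visits, r from 0.3 to 0.7, and a week-26 difference of 1.5 or 3.0. Two-sided power at 67 per group then runs from about 52% (r = 0.7, week-26 difference 1.5) to about 86% (r = 0.3, week-26 difference 3.0).

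**The case against.** The strongest reply is that section 12.3 never says two-sided and does not mention an F-test. The only statement on sidedness in the protocol is in 12.1. It is phrased as how testing will be done, and 12.3 repeats the same 0.05. Read together, the two sections can describe a one-sided 0.05 test inside an ANOVA. A one-degree-of-freedom effect can be tested as a signed t-contrast, and power at 67 per group is then 79.5%, in line with the plan. How such a contrast is extracted is often left to an analysis plan, and none is shown here.

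Much of this stands. A reader might infer that the planned test is two-sided and that the trial's true power is 67 to 69%. The documents do not support that as a fact. The loss occurs only if the ordinary F-test is used, and the 67% end also needs the separate dropout shortfall. Nor is the sample-size calculation wrong in itself: 67 follows from its stated inputs. If every enrolled patient is analysed, as the protocol's references to intention to treat suggest, two-sided power is about 77%; section 10.3 is itself unclear on whether patients whose code is broken are included.

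What the reply does not remove is the mismatch. The protocol names both a directional test and a procedure whose default test has no direction, and supplies no link between them. An analysis plan could follow one only by departing from the other or by adding a step that the protocol does not mention.

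**Conclusion.** The point holds in conditional form. Section 12.1 fixes a one-sided 0.05 basis and section 12.3 does not carry it into the ANOVA. If the ordinary F-test is used on baseline-to-week-52 change with difference 3.0 and SD 7.0, power falls about 10 percentage points at the stated size, to 69%. It stays below 80% even with all 80 per group analysed. If a signed contrast is used, power at 67 is essentially as stated.

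The disagreement over the success threshold applies only to results that favour indomethacin; a difference in the harmful direction with a two-sided p between 0.05 and 0.10 is not a success under either test. All the power figures rest on time meaning baseline and week 52. On the weeks 26 and 52 reading, power cannot be fixed from the protocol, although the F-test remains non-directional.

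**What to change.** State one primary test, in the same terms, in sections 12.1 and 12.3 before unblinding, and say which visits define time. Either option resolves the conflict:

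- **(a) Keep one-sided 0.05.** Section 12.3 names a directional contrast on change from baseline to week 52 in place of an unspecified ANOVA test. Power is about 79 to 80% at 67 evaluable per group, and about 78% at the 64 left after 20% dropout from 80.
- **(b) Declare the test two-sided at 0.05 with a 95% confidence interval.** Section 12.1 restates power for 3.0 points as about 69% at 67 evaluable per group, and about 67% at 64, where the difference detectable with 80% power is about 3.5 points.

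The cost is wording in two sections and, under (b), a less favourable stated power. Neither option adds patients or changes any assessment.
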